**Methods:**

This pragmatic trial is designed as a prospective, three-armed randomised controlled trial in a clinical setting provided at a general hospital physiotherapy department. Two hundred ninety-seven participants with a diagnosis of migraine, TTH or CGH based on published headache classification guidelines will be included. An assessor blind to group allocation will measure outcomes pre-and post-intervention as well as 3 and 6 months after commencement of treatment. Participants will be allocated to one of the three groups: MMT and exercise; placebo and exercise; and exercise alone. The primary outcome measure is headache frequency. Secondary outcome measures are headache duration and intensity, medication intake, pressure pain threshold (PPT), range of motion recorded with the flexion rotation test, and headache disability recorded with Headache Activities of Daily Living Index (HADLI). The intention-to-treat principle will be followed for statistical analysis. Between groups differences for all outcome measures at baseline and at reassessment points and 95% confidence intervals will be calculated using a mixed model ANOVA. Post hoc tests will be conducted to identify any significant difference between groups and over time.

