### Procedures

Participants will be provided with an information sheet outlining the study protocol including duration of commitment, intervention, benefits and harms of the treatment, voluntary participation, right to withdraw, as well as confidentiality of data. It will be explained that no compensation will be given if any adverse event occurs and study findings may be published but without revealing participants identity.

Those willing to participate will be enrolled and asked to provide signed written informed consent with the right to withdraw at any time. After recruitment, at initial assessment, a qualified therapist will explain the study procedures and collect demographic data. Confidentiality will be maintained throughout the trial.

Participants will then be randomly and equally allocated to one of three groups: MMT plus exercise; placebo plus exercise; or exercise alone by stratified randomization based on the type of headache. Randomization will be achieved using a computer-generated sequence received in advance from an independent statistician and will be hidden in sequentially numbered opaque sealed envelopes by a research assistant. All participants will be asked to not reveal their group identity and are advised to continue with their regular medical management. Any change in the protocol will be communicated with the ethics committee and if approved appropriate changes will be made in the Clinical Trial Registry.

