C1-C2 SNAG: If the subject does not present with a headache at the time of the assessment, the flexion-rotation test (FRT) [45] will be evaluated. If a 10° restriction is identified compared to the reference standard of 44°, a unilateral posteroanterior mobilisation will be applied to the transverse process of the first cervical vertebrae on the contralateral side of restriction on the FRT. The subject will be asked to rotate the head towards the restricted side of the flexion-rotation test as far as they are able without pain. A maximum of 3 repetitions will be applied in a single treatment session. If impairment is not identified on the FRT and there is no headache symptoms present, then only exercise will be provided as there is no further option for treatment using MMT.

The third group will receive a placebo replicating the Headache SNAG technique but without any manual force applied. The position will be held for 10 to 30 s and 6 repetitions applied. The duration of the placebo treatment session will be similar to that in the MMT group. Participants will continue to receive the same exercise protocol as the other groups. Any increase in headache intensity or neck pain for more than 1 h or dizziness during or after the intervention will be documented as an adverse event. In such cases, participants will be referred to a medical practitioner of the hospital and withdrawn from the study.

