### Outcomes

Outcome measures will be taken at base line just after enrolment, as well as at 4 weeks, 3 months and 6 months following treatment commencement by an assessor, blind to group allocation and intervention. To assess whether the participants were blind to intervention or not, after each treatment session the participants in the MMT and the placebo group will complete a questionnaire on whether they believed MMT treatment was received, partly received or not.

The primary outcome measure is headache frequency [46] which is the total number of headache days per month noted in a headache diary. Secondary outcome measures are as follows: headache intensity [47] recorded on a 10 cm visual analogue scale, which is considered a valid and reliable tool for measuring pain intensity [47]. Headache duration [46] will be measured in hours per week. Headache frequency and duration are considered a valid method of measurement in the headache population [46]. Medication Intake will be recorded as total tablets consumed per week. PPT will be measured using a digital algometer with a surface area of 1 cm kg/cm^2^, with pressure applied at the rate of 1 kg/ cm^2^ /s perpendicular to the skin. PPT will be assessed over the suboccipital muscles, C2–3 zygapophyseal joint and upper trapezius muscle bilaterally [48] to assess local hypersensitivity, and over the tibialis anterior muscle to assess central sensitisation. Reliability for measuring PPT was reported as excellent (ICC: 0.82–0.99) [49]. Headache disability will be recorded with the Headache Activities of Daily Living Index (HADLI) [50] which is a 9 item self-reported questionnaire designed to measure the impact of headache on quality of life. Each item has 6 sub-questions which are rated from 0 to 5 thus the maximum score of 45 indicates a severe disability. Patient satisfaction will be assessed using a 0–100% numeric rating scale. Passive upper cervical rotation range in degrees to both sides will be measured with the FRT using a previously reported reliable and valid method [45]. A compass application on a smart phone mounted on the patient’s head with Velcro straps will be used to measure range of motion. Reliability of the FRT was reported as good to excellent in subjects with migraine (0.71–0.78) and CGH (ICC: 0.73–0.83) [51].

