### Statistical methods

The sample size for this study was calculated based on the primary outcome of headache frequency. According to the International Headache Society guidelines (2018), a 50% reduction in headache frequency is considered a clinically significant difference. A sample size of 297 participants will be required for the study based on a priori power analysis with a power of 0.8 and an alpha of 0.05 assuming 10% drop-outs.

All data entry will be carried out by research assistants who will be blind to treatment allocation. The final trial dataset will be accessible to all investigators and a statistician. Data will be stored with the principal investigator. Descriptive statistics will be performed to examine baseline parameters and demographic data. Demographic data will include age, gender, symptom duration, occupation, height, and weight. Baseline parameters will include the headache frequency, intensity, duration, medication intake, PPT, HADLI score, and FRT range of motion. Parametric tests will be used for normal distributions and ratio level data. Between groups differences for the primary and secondary outcome measures at baseline and at reassessment points and 95% confidence intervals will be calculated using mixed ANOVA. Post hoc tests will be conducted to identify any significant difference between groups and over the time. The intention-to-treat principle will be used if loss of follow up is not more than 10%. Non-parametric tests will be applied for non-normal distributions and ordinal level data.

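### Intention-to-treat analysis is conditional on loss of 10% or less in the Statistical methods but unconditional in the Abstract, and no analysis set is named above 10%

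*Protocol article*

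**What the plan says.** The protocol article describes the analysis population in two places.

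- **Abstract, Methods:** "The intention-to-treat principle will be followed for statistical analysis". No condition is attached.
- **Statistical methods:** "The intention-to-treat principle will be used if loss of follow up is not more than 10" per cent. Nothing is said about the analysis set or method if loss is greater.

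Three other statements bear on the point.

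- The total of 297 is described as "based on a priori power analysis with a power of 0.8 and an alpha of 0.05 assuming 10% drop-outs", so the drop-out allowance and the threshold are the same figure.
- Outcomes are measured at baseline, "as well as at 4 weeks, 3 months and 6 months following treatment commencement", so loss can build up over six months.
- Under Interventions, a participant with a documented adverse event is handled as follows: "participants will be referred to a medical practitioner of the hospital and withdrawn from the study". Participants who receive other physical treatment to the neck or shoulder are also withdrawn.

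No other section reconciles the two statements.

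**The concern.** Randomisation protects the three-arm comparison when participants are analysed in the groups to which they were allocated. The Statistical methods rule guarantees that only while attrition is low, when an as-randomised set and a reduced set nearly coincide and the choice matters little. Once attrition is high enough for the sets to diverge, the guarantee lapses. The rule therefore runs in the wrong direction.

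It also makes the primary population depend on observed loss, which is known only after randomisation and may be related to treatment and response. Adverse events and the use of other physical treatment may differ between an arm receiving manual force, a placebo arm without force and an exercise-only arm. With no alternative named above 10%, the set would have to be chosen after the pattern of loss is known.

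**Working it through.** **1. The two statements compared**

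| Observed loss | Abstract | Statistical methods |
|---|---|---|
| 10% or less | intention-to-treat | intention-to-treat |
| above 10% | intention-to-treat | not assured; nothing named |

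The conflict is confined to the second row, the only case in which the condition has any effect.

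**2. The plan's own figure**

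The base sample size cannot be reproduced. The article gives no standard deviation, between-group difference, test or sidedness, only that "a 50% reduction in headache frequency is considered a clinically significant difference". The drop-out step alone can be checked:

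- 89 per arm × 3 = 267 evaluable; 267 / 0.9 = 296.7, rounded up to 297.
- 90 per arm × 3 = 270 evaluable; 270 × 1.1 = 297.

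Either route gives 297. Allocation is equal, so 297 / 3 = 99 per arm.

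**3. Where the threshold falls**

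- 29 / 297 = 9.8%: intention-to-treat is kept.
- 30 / 297 = 10.1%: the condition fails.

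**4. How likely it is to be crossed**

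Let X be the number lost, with X ~ Binomial(297, p) and p the true loss rate. The condition fails when X ≥ 30. The 10% rate is the article's planning figure; the other rates are assumed, to show the range.

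| True loss rate p | P(X ≥ 30) |
|---|---|
| 5% | 0.0002 |
| 8% | 0.11 |
| 10% (planning figure) | 0.51 |
| 12% | 0.86 |
| 15% | 0.99 |

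This assumes independent losses at a common rate, counted overall at the final visit. The article does not say whether loss is counted overall, per arm or per visit, or whether withdrawn participants count as lost.

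**5. Effect of removing the condition**

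No sample-size figure changes. The probability that the population rule lapses because of attrition becomes 0 at every loss rate.

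**The case against.** Several arguments can be made on the other side.

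- **A reader might infer that the Abstract says the opposite of the Statistical methods.** It does not. One statement is unconditional and the other conditional, and they agree at 10% loss or less. The conflict above 10% stands.
- **A reader might infer that the protocol moves the primary analysis to a per-protocol or completers' set above 10%.** Giving up intention-to-treat is the natural implication, but no such set is named. In a condensed article the sentence could even be shorthand for when missing values will be imputed. What is documented is that the analysis above 10% is left open.
- **A reader might size the harm as a shift in an arm's mean caused by selective loss, set against the difference the trial can detect.** The documents do not support this. Such a shift comes from missing outcomes, and both the current rule and the corrected one would leave it in place when loss depends on unobserved outcomes. The detectable difference would also have to be assumed, because the article gives no standard deviation or between-group difference.
- **The drop-out figure is a planning allowance and need not be a forecast.** This is fair. If true loss is 5% or 8%, the threshold is unlikely to be crossed, so the full range is shown.
- **Missing-data methods are usually left to the statistical analysis plan.** That is true of the choice of model and of sensitivity analysis. The condition itself is a rule fixed in this article. An analysis plan could follow one of the two statements above 10% only by departing from the other.

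**Conclusion.** The point holds in this form: the condition in the Statistical methods is wrong as written and inconsistent with the Abstract. Followed literally, it stops assuring analysis as randomised when selective loss matters most, and it leaves the primary population undefined in advance.

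How often this would matter depends on the true loss rate. It is about an even chance at the article's own 10% allowance, very unlikely at 5%, and close to certain at 15%. These figures rest on independent losses counted overall among 297. No estimate of bias in the treatment effect can be drawn from the documents.

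**What to change.** 1. Delete the 10% condition from the Statistical methods so that the section matches the Abstract.
2. State that the primary analysis includes every randomised participant in the allocated group, whatever the loss to follow-up, using all available follow-up data. A likelihood-based mixed model would do this. A complete-case mixed ANOVA would not, because it discards anyone with a missing visit. The Abstract refers to a mixed model ANOVA and the Statistical methods to a mixed ANOVA, so the text should say which is meant.
3. If loss exceeds 10%, add a missing-data sensitivity analysis and leave the population unchanged. If 10% is kept as the trigger, state how loss is counted and whether withdrawn participants are included.
4. Label any per-protocol analysis as supplementary.

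The cost is a short change of text and a little more analysis work; the sample size is unaffected. The change makes the primary population known in advance, but does not by itself remove bias from loss that depends on unobserved outcomes, which is why the sensitivity analysis is needed.

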## Discussion

To our knowledge, this will be the first pragmatic RCT to evaluate the effects of MMT in the management of migraine, TTH and CGH. A pragmatic effectiveness study design will enable a greater understanding of the true effect of MMT when compared with a placebo intervention and a control group in reducing various parameters of headache over a 6 months period. A placebo effect is associated with all physiotherapy interventions however its contribution may vary. This study will help us to understand the true net effect of MMT over placebo.

Recruitment will be a challenge due to the strict inclusion criteria but that could be strength of our study to involve a homogeneous population of headache sufferers with features of upper cervical articular dysfunction who might respond to MMT.

Previous studies using MMT targeting the upper cervical spine for headache management have not reported adverse events associated with its application. Thus this approach appears to be safe for its clinical use [52]. All participants will continue to take their medications as prescribed by their medical practitioner.

Several limitations of the study protocol must be discussed. Headache differentiation into one of three categories will be challenging due to the overlap of features among headache forms. The medical practitioner’s experience in differential diagnosis may help to overcome this. Baseline evaluation of headache parameters may be affected by recall bias, this is inevitable when recalling headache, but would be the same for each headache group. A further issue is that generalisation of results may only be limited to the headache population with a minimum 1-year history of headache. Headache is a chronic disease and the use of non-pharmacological management in those with headache for less than 1-year is not common practice in our hospital facility. All treatments will be delivered by one therapist possibly creating a performance bias. However, the therapist will ensure that each intervention is applied with equal emphasis and confidence. In addition, all subjects will be asked if they received the intervention which may provide a measure of performance bias. The home exercise programme is unsupervised but compliance will be evaluated with an exercise diary. The HADLI questionnaire is not yet extensively evaluated for its psychometric properties but studies are currently underway to evaluate those properties. Lastly, the outcome measure PPT lacks standardization, cannot be used in diagnosis or screening [53], and has no association with other headache parameters [49]. However, PPT is included to assess local and peripheral hypersensitivity which is one of the common features of central sensitisation [54]. The effect of MMT on local and peripheral hypersensitivity has been measured indirectly with PPT in other peripheral musculoskeletal conditions, for example at the knee joint [55].

The study will contribute to the evidence base for manual therapy management of headache and will lead to improved clinical decision making in the field of non-pharmacological management of headache.

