**Discussion:**

This pragmatic study will provide evidence for the effectiveness of MMT when compared with a placebo intervention and exercise on headache frequency, intensity, and disability. Limitations are that baseline evaluation of headache parameters may be affected by recall bias. External validity will be limited to the population with a minimum 1-year history of headache. The HADLI is not yet extensively evaluated for its psychometric properties and association between PPT and headache parameters is lacking. Performance bias is inevitable as a single therapist will be delivering all interventions.

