This paper aims to report the study protocol which will be used to investigate the short and mid-term effectiveness of MMT and exercise on headache frequency, intensity, disability, and duration as well as medication intake, upper cervical rotation range of motion, PPT and patient satisfaction compared with placebo and exercise and exercise alone in the management of migraine, TTH, and CGH. The objective is to investigate whether MMT with exercise is more effective than placebo MMT with exercise or exercise alone. Our primary hypothesis is that there will be a 50% reduction in headache frequency in the experimental group (MMT with exercise) and recovery is greater than that seen in the 2 control groups (placebo MMT with exercise and exercise alone).

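### Baseline headache frequency appears to be recalled and follow-up frequency diary-recorded, so the within-arm 50% reduction in the primary hypothesis mixes two instruments; the randomised comparison is not biased

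*Protocol article*

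**What the plan says.** Five places in the Protocol article bear on this.

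- **Outcomes, definition.** The primary outcome is "headache frequency [46] which is the total number of headache days per month noted in a headache diary".
- **Outcomes, timing.** "Outcome measures will be taken at base line just after enrolment", and then "as well as at 4 weeks, 3 months and 6 months following treatment commencement". No diary period before treatment is described.
- **Abstract (Discussion) and Discussion.** The abstract states: "Limitations are that baseline evaluation of headache parameters may be affected by recall bias". The main Discussion states: "Baseline evaluation of headache parameters may be affected by recall bias, this is inevitable when recalling headache". It offers one mitigation, that the bias is present "but would be the same for each headache group".
- **Background, last paragraph.** The primary hypothesis has two parts. The first is that "there will be a 50% reduction in headache frequency in the experimental group (MMT with exercise"). The second is that recovery in that arm exceeds recovery in the two control arms.
- **Statistical methods.** A 50% reduction is named as the clinically significant difference. Between-group differences at baseline and at the reassessments are to come from a mixed ANOVA, with post hoc tests between groups and over time.

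**The concern.** A diary handed out at enrolment cannot supply the month before enrolment. Taken with the recall-bias statements, this means that the baseline does not meet the document's own definition of the primary outcome, while the later values do. A fall from baseline to follow-up then contains the true change plus the shift from memory to diary.

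Randomisation does not remove that shift, because it lies between time points and not between arms. The stated mitigation does not remove it either. An error shared by all groups moves every within-group reduction in the same direction. Read literally, the mitigation also speaks of headache diagnoses, not of treatment arms or of baseline against follow-up.

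At stake are the first half of the primary hypothesis and those post hoc tests over time that use baseline. Either could show, or fail to show, a 50% fall for reasons unrelated to treatment. Tests among the 4-week, 3-month and 6-month values compare diary with diary and are unaffected.

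**Working it through.** **1. The plan's own figure.** The total is 297, with power 0.8, alpha 0.05 and 10% drop-outs. The drop-out step is possible: 267 / 0.9 = 296.7, rounded up to 297, or 89 evaluable per arm. The 267 itself cannot be derived, because no SD, control-arm value or responder rate is given. Solving backwards for two means at two-sided 0.05 gives (1.960 + 0.842) × √(2/89) = 0.42 SD. That figure is back-solved and is not in the document. The present point neither confirms nor refutes 297.

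**2. Within-arm reduction.** Let t be the true proportional reduction and b the ratio of recalled to true mean baseline (b = 1 means no error). With diary follow-up,

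apparent reduction = 1 − (1 − t)/b.

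The document gives no value of b, so a range is assumed.

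| b | True 0% appears as | True 40% appears as | True 50% appears as | True reduction needed to show 50% (1 − 0.5b) |
|---|---|---|---|---|
| 0.8 | 25% increase | 25% | 37.5% | 60% |
| 0.9 | 11% increase | 33% | 44% | 55% |
| 1.0 | 0% | 40% | 50% | 50% |
| 1.1 | 9% | 45% | 55% | 45% |
| 1.2 | 17% | 50% | 58% | 40% |
| 1.3 | 23% | 54% | 62% | 35% |

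Example: t = 0.40 and b = 1.2 gives 1 − 0.60/1.2 = 0.50. At b = 0.8 it gives 1 − 0.60/0.8 = 0.25.

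**3. Between-arm comparison.** If recall error is independent of arm, its mean cancels in the difference between arms in days. A simulation checked this with 89 per arm, an assumed true baseline of about 9 days per month (SD 3), b = 0.8, 1 and 1.25, and recall noise of zero or 30% on the log scale.

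- True reductions of 50% v 35%: the expected difference is 9 × 0.15 = 1.35 days. The simulated difference in change lay between −1.335 and −1.368 days in all settings.
- True reductions of 40% v 40%: the difference was close to 0, and the type I error was 0.041 to 0.060 against a nominal 0.05.

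On a percentage scale the null is still preserved, but the size is rescaled to (t₁ − t₂)/b. A true gap of 15 points shows as 15/0.8 = 18.75 or 15/1.25 = 12 points.

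**4. How baseline enters the analysis.** Assume equal variance σ² at both times and a baseline-to-follow-up correlation of 0.3.

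- Change score: variance 2(1 − 0.3)σ² = 1.40σ². z = 0.42/√(2 × 1.40/89) = 2.37, so power is Φ(2.37 − 1.96) = 0.66.
- Baseline as covariate: variance (1 − 0.3²)σ² = 0.91σ². z = 0.42/√(2 × 0.91/89) = 2.94, so power is Φ(2.94 − 1.96) = 0.84.

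These figures compare two analyses of the same data. They do not measure what recall costs relative to a diary.

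**The case against.** The case on the other side has several parts.

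- **The change of instrument is inferred.** No sentence sets recall at baseline against diary at follow-up, and the full protocol and the flow chart are not shown. This is correct. The reading rests on the outcome definition, the baseline timing and the two recall-bias statements taken together, and no other reading fits them as naturally.
- **A reader might infer that the trial's treatment comparison is biased.** The documents do not support that. Procedures places allocation after the initial assessment, baseline is taken just after enrolment, and the check above shows no bias in days. Statistical methods plans between-group differences and names no percentage change or responder analysis. The second half of the hypothesis is comparative and survives.
- **A reader might infer that recall lowers power from 0.84 to 0.66.** It does not follow. That contrast is between analysis of covariance and a change score under assumed inputs.
- **A within-arm fall is weak evidence in any case.** Entry requires pain above 6 and at least weekly headache, all arms exercise, and usual medication continues. Regression to the mean and these other influences would enter even with a perfect diary baseline. This stands: recall is one contributor among several, and it is a further reason not to judge the 50% criterion within one arm.
- **Recall bias is disclosed.** It is, but its effect on the 50% criterion is not. The Discussion can fairly be read as saying only that bias comes with recall, not that a recalled baseline is unavoidable, so the word needs no correction.

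**Conclusion.** The point holds in a limited form. The natural reading is a recalled baseline against a diary-defined outcome. On that reading, the 50% reduction within the MMT-plus-exercise arm, and post hoc tests of baseline against follow-up, cannot be separated from the change of instrument. Under an assumed recall error of −20% to +30%, a true 40% fall appears as anything from 25% to 54%, so the 50% mark can be created or missed. The direction and size of the real error are unknown.

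The randomised between-arm difference in headache days is not biased, provided that baseline is recorded before allocation, as the order of Procedures indicates. There the cost of recall is noise, and it falls mainly on analyses built on change from baseline. The repair is worth making because it costs little and protects the conclusion the trial can support.

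**What to change.** **Analysis.** Make the primary inference the between-arm difference in diary headache days at follow-up, adjusted for baseline frequency as a covariate. Do not enter baseline as a repeated level of the outcome, and do not analyse a change score. A recalled baseline is a legitimate covariate even though it comes from another instrument. Much of this fits the between-group comparisons already planned; what is added is the role of baseline.

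**Hypothesis.** Restate the primary hypothesis as a comparison: fewer follow-up diary headache days with MMT plus exercise than with each control. Make no within-arm 50% reduction or responder claim against the recalled baseline, and do not interpret post hoc tests of baseline against follow-up as treatment effects.

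**Limitations.** Add that baseline and follow-up appear to use different instruments, and that equal recall error across headache groups protects comparisons between groups but not change over time. If baseline does in fact come from a diary, say so in Outcomes and correct the recall statements.

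**Cost.** Analysis and reporting wording only, and the loss of the within-arm 50% statement.

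**Optional.** A diary period before randomisation, for example 4 weeks, would put baseline on the same instrument as follow-up. It would delay treatment, may lose some screened patients, would affect eligibility if also used for the weekly-frequency criterion, and needs ethics approval and a registry change. The sponsor must weigh that trade-off; the minimum fix does not depend on it.
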